**Methods:**

The LIBERATE study will be a multicenter, parallel-group, blinded, randomized placebo-controlled trial. It will recruit adult (i.e., age ≥ 18 years) critically ill patients receiving stable or decreasing doses of IV vasopressors. Eligible patients will be randomized to receive either midodrine 10 mg administered enterally every 8 h or placebo until 24 h post-discontinuation of IV vasopressors. The primary outcome will be ICU length of stay. Secondary outcomes include all-cause mortality at 90 days, hospital length of stay, length of IV vasopressor support, re-initiation of IV vasopressors, rates of ICU readmission, and occurrence of AEs. Health economic outcomes including ICU, hospital and healthcare costs, and cost-effectiveness will be evaluated. Pre-planned subgroup analyses include age, sex, frailty, severity of illness, etiology of shock, and comorbid conditions.

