## Methods

### Study design

The LIBERATE trial is a multicenter, concealed-allocation parallel-group blinded placebo-controlled randomized trial. The trial will randomly allocate 350 critically ill adult patients receiving IV vasopressor therapy to either midodrine 10 mg or identical placebo. This dose was chosen based on the product monograph suggested dosing. The investigational product will be administered enterally every 8 h for the duration of their IV vasopressor therapy and up to 24 h after discontinuation of their IV vasopressor therapy. Table 2 shows a timeline of trial activities. The SPIRIT checklist is available in Additional file 2.

**Table 2 Tab2:** Trial activity timeline

Time points		Study period			
	Enrollment	Post-enrollment			
	Day 1	Days 2–30	ICU/hosp discharge	Month 6	Month 9
Enrolment					
Eligibility screen	x				
Informed consent	x				
Treatment allocation	x				
Intervention					
Midodrine or placebo	x				
Assessments					
Age, sex	x				
Weight and height	x				
Date of eligibility	x				
ICU and hospital admission date	x				
ICU admission type	x				
ICU admission diagnosis	x				
Clinical frailty scale score	x				
APACHE II score	x				
Etiology of shock	x				
Comorbid illness	x				
Vasopressor therapy	x	x			
Mechanical ventilation	x	x			
Total duration of vasopressor support			x		
Vasopressors initiated after cessation		x			
ICU or hospital death		x			
Date of ICU death or discharge		x			
ICU length of stay			x		
Hospital length of stay			x		
ICU readmission during hospital stay			x		
Discharge location from hospital			x		
Persistent organ dysfunction or death				x	x
EQ-5D					x
Adverse events	x	x	x	x	x
Cardiac events (clinically significant bradycardia, acute coronary syndrome)	x	x	x	x	x
Allergic events (paresthesia, piloerection, dysuria, pruritis, chills, pain, rash)	x	x	x	x	x
Hypertension	x	x	x	x	x
Bowel ischemia	x	x	x	x	x
Limb ischemia	x	x	x	x	x
Stroke	x	x	x	x	x
Protocol violations	x	x	x	x	x

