### Randomization

Randomization will be done as per a computer-generated randomization schedule through a Web-based portal (i.e., Randomize.net). Eligible patients will be randomized in a 1:1 ratio to midodrine or placebo using permuted blocks of undisclosed and variable size. We will stratify randomization by site.

Randomization will be conducted by the study pharmacists after receiving written notification of the patient enrollment from the study team. The study pharmacy will then prepare and dispense the appropriate blinded study treatment.

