### Statistical analyses

All patients will be analyzed as randomized in accordance with the intention-to-treat principle. However, we will also plan a secondary efficacy analysis including patients who received all study drug doses (per protocol analysis). The criterion for statistical significance will be based on alpha = 0.05. All tests will be two-sided, and all analysis will be performed using STATA v16 or later.

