### Data analysis

#### Patient-centered analysis

All analyses will follow the intention-to-treat (ITT) principle. Analyses of the primary and secondary outcomes (i.e., patient-centered outcomes) will involve summary measures obtained by aggregating the endpoints using Stata software package (StataCorp, TX, USA). We will compare median differences along with their 95% confidence intervals. Baseline comparisons will be performed using the chi-squared test for equal proportions with results to be reported as numbers, percentages, and 95% confidence intervals. Continuous normally distributed variables will be compared using paired *t*-tests and reported as means with 95% confidence intervals, while non-normally distributed will be compared using Wilcoxon rank sum tests and reported as medians and interquartile ranges.

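### The protocol names paired t-tests for comparing two independent parallel arms: a wording error that should be corrected, though it probably spares the primary result

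*Protocol article*

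**What the plan says.** The design is stated consistently. The abstract describes a "multicenter, parallel-group, blinded, randomized placebo-controlled trial", and the study design section a "concealed-allocation parallel-group blinded placebo-controlled randomized trial". On allocation, the randomization section says: "Eligible patients will be randomized in a 1:1 ratio to midodrine or placebo using permuted blocks of undisclosed and variable size". It adds: "We will stratify randomization by site". No section describes matched patients, a crossover, or a within-patient contrast between treatments.

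The patient-centered analysis section then gives the tests for continuous variables. For the normal case: "Continuous normally distributed variables will be compared using paired" *t*-tests. In the same sentence, for the other case: "non-normally distributed will be compared using Wilcoxon rank sum tests". The sentence comes directly after the one on baseline comparisons by chi-squared test. Before both, the section says that median differences with 95% confidence intervals will be compared.

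The general rules are in the statistical analyses section: "The criterion for statistical significance will be based on alpha = 0.05", and "All tests will be two-sided".

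**The concern.** A paired *t*-test analyses differences within pairs, and each pair must be defined by the design. Here a patient belongs to one arm only. Stratifying by site and allocating in blocks balances the numbers in each arm, but does not tie one midodrine patient to one placebo patient.

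To run the test as written, an analyst would have to join unrelated patients, in practice by their order in the file. Two consequences follow.

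- The standard error, and with it the p-value and the confidence interval, would depend on how the data happen to be sorted. With equal arms, the difference in means would not change.
- If the arms differ in size, the surplus patients in the larger arm would have no partner and would drop out of a comparison that is declared to be by intention to treat. Unequal arms are quite possible: the protocol allows up to 8% loss to follow-up, withdrawal without replacement, and certain post-randomization exclusions.

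**Working it through.** **1. Consistency of the text.** The abstract, the study design section and the randomization section all describe independent arms. Within the disputed sentence, the rank sum test assumes independent groups; its counterpart for paired data would be the signed-rank test. One half of the sentence therefore treats the arms as paired and the other half as independent. Only the independent half fits the design.

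**2. The plan's own figures.** The sample size section gives 161 per arm before loss and allows for 8% loss: 161 / (1 − 0.08) = 175.0, so 175 per arm and 350 in total reproduce. The 161 itself cannot be checked, because no standard deviation is given. For the simulations below it was assumed to come from the usual two-means formula, which implies a standardised effect of (1.960 + 0.842) × √(2/161) = 0.312. For a 20% reduction, that is a standard deviation of about 0.2 / 0.312 = 0.64 of the control mean.

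**3. How row order enters.** Take n per arm and equal variances s². Let r be the sample correlation between the rows that happen to be joined.

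- Unpaired: SE = s√(2/n), with 2n − 2 degrees of freedom.
- Paired: SE = s√(2(1 − r)/n), with n − 1 degrees of freedom.
- Hence t(paired) = t(unpaired) / √(1 − r).

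Under random ordering, r has mean 0 and standard deviation 1/√(n − 1). For n = 161 this is 0.079, so r lies within about ±0.155 in 95% of orders. Take data with unpaired p = 0.050, so t = 1.967 on 320 degrees of freedom:

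| r | t(paired), 160 df | paired p |
|---|---|---|
| +0.155 | 1.967/√0.845 = 2.140 | 0.034 |
| −0.155 | 1.967/√1.155 = 1.831 | 0.069 |

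Simulation agrees. For one such data set with 161 per arm, 10,000 random row orders gave a central 95% of paired p from 0.034 to 0.069, and a full range from 0.020 to 0.091. With 175 per arm and 5,000 orders, the central 95% was 0.035 to 0.069.

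**4. Rows that are not in random order.** In the same data set with 161 per arm, sorting both arms by the outcome gave p of about 4 × 10⁻⁶⁵. Sorting them in opposite directions gave p = 0.17, which matches the formula at r near −1: 1.967/√2 = 1.391, p = 0.17.

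**5. Degrees of freedom.** With 175 per arm they are 174 (paired) against 348 (unpaired). The two-sided 5% critical value moves only from 1.967 to 1.974.

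**6. Long-run behaviour with arbitrary pairing** (normal data, 161 per arm, 20,000 simulated trials):

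| | Paired | Unpaired |
|---|---|---|
| Type I error | 5.06% | 5.03% |
| Power at effect 0.312 | 79.6% | 79.8% |

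At the design effect the two tests disagreed on significance in 1.9% of trials. A separate simulation gave type I error of 4.9% for both tests, power of 79.5% against 79.8%, and disagreement in 1.8%.

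**The case against.** The case for treating this as minor is strong, and most of it stands.

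- **Scope.** The sentence speaks of variables, not outcomes, and follows directly on the baseline comparisons. It may be meant mainly for the baseline table. This stands as a limit on the point, but a paired test between arms is wrong for baseline variables too, and the sentence exempts no outcome.
- **Primary outcome.** The primary outcome is ICU stay in hours, and the continuous patient-centered secondary outcomes are also durations. Such variables are usually right-skewed, and a standard deviation near 0.64 of the mean would be consistent with that. They would then go to the rank sum test, which is valid here. This stands, as a likelihood: the choice of test is left to a judgement of normality.
- **Drafting slip.** Naming the rank sum rather than the signed-rank test suggests that the authors had independent groups in mind and meant unpaired. This is plausible. It makes the correction easy but does not make the text right.
- **Size.** With arbitrary pairing, the error rates barely move. This stands.

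A reader might go further and infer that the primary analysis is invalid, or that about half of results could turn on file order. The document does not support either. The first ignores the route to the rank sum test. The second comes from data built to sit exactly at p = 0.050 (46% to 47% of row orders fell below 0.05), where any small perturbation splits the results roughly in half. Nor are the degrees of freedom arbitrary: they are fixed at the number of pairs minus one.

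**Conclusion.** The sentence is wrong as written. It names a specific test that the design cannot support, and its own second half contradicts it. This is an error in a stated rule, not detail left to an analysis plan that is not shown.

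Its practical weight is modest. It applies to any continuous variable judged normal, possibly mainly baseline variables, and the primary result is probably spared. Where it does apply, the harm is a p-value and interval that cannot be reproduced without knowing the row order, extreme results if the file is sorted by outcome, and loss of patients when arm sizes differ. It does not systematically inflate type I error or cost appreciable power: the tests disagree in about 2% of trials at the design effect.

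These figures assume normal data, equal variances, equal arms and random row order except where sorting is stated. The power and disagreement figures also rest on the effect size back-calculated from 161 per arm. The finding that the test does not fit the design rests on none of these assumptions. It should be corrected, but it is no threat to the trial as a whole.

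**What to change.** In the patient-centered analysis section, replace paired *t*-tests with independent two-sample *t*-tests. It would help to say in the same line whether the sentence covers baseline variables, outcomes, or both.

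The cost is one line of wording, with no change to data collection or to the planned 350 patients. It is best made before database lock and unblinding, so that the change cannot be read as a choice of test made after seeing results. An unequal-variance version, a model with site, or fixing the rank-based test for durations in advance are separate preferences; this correction does not need them.

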### Study setting

The study will be centrally coordinated by the Research Office in the Department of Critical Care Medicine at the University of Alberta Hospital. The study will be performed at 7 mixed medical/surgical ICUs throughout Alberta. Additional sites outside of Alberta may be added, as necessary.

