### Sample size

Using an alpha of 0.05 and a power of 80% and assuming a 20% deduction in the length of stay associated with midodrine based on previous pilot work by Anstey et al., we would need a sample size of 161 patients per arm [20]. To compensate for up to an 8% loss to follow-up, we will plan for 175 patients per arm for a total treatment size of 350 patients.

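### Randomisation is stratified by site, but the comparisons named for a skewed outcome such as ICU stay use neither site nor baseline APACHE II; the test stays valid, and some precision is forgone

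*Protocol article*

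**What the plan says.** All references are to the protocol article.

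- **Randomization:** 1:1 allocation in permuted blocks of varying size. "We will stratify randomization by site". No other stratification factor is named.
- **Study setting:** "The study will be performed at 7 mixed medical/surgical ICUs throughout Alberta", with further sites possible.
- **Primary outcome measure:** ICU length of stay in hours, recording both the discharge decision and the actual departure.
- **Patient-centered analysis:** outcomes are compared by median differences with 95% confidence intervals. After a sentence on baseline comparisons, the section adds that continuous variables that are "non-normally distributed will be compared using Wilcoxon rank sum tests and reported as medians and interquartile ranges". It names no stratified test, site term or covariate.
- **Study design, Table 2:** the "APACHE II score" and the Clinical Frailty Scale are collected on day 1. In the analysis sections they appear only under Pre-specified subgroup analyses.
- **Statistical analyses and Sample size:** "The criterion for statistical significance will be based on alpha = 0.05"; "All tests will be two-sided". The 161 per arm is for 80% power, "assuming a 20% deduction in the length of stay associated with midodrine", raised to 175 for 8% loss.

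**The concern.** Blocking within site forces the arms to be balanced on site. If stay differs between sites, the treatment difference then varies less from trial to trial than an ordinary two-sample standard error assumes. An analysis that ignores site uses a standard error that is too large: its intervals are too wide and its true type I error falls below the nominal level.

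Baseline severity is a separate matter. APACHE II is not a stratification factor, so omitting it leaves type I error where it is. The cost is unused precision if severity predicts ICU stay.

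At stake is efficiency, and agreement between design and analysis, in a trial sized at 80% power. False positives are not at stake.

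**Working it through.** **Plan's own figure.** The loss step reproduces: 161 / (1 − 0.08) = 175. The 161 cannot be derived, because the article gives no SD or control value for stay. It can be back-solved: standardised effect = (1.960 + 0.842) × √(2/161) = 0.312. If the 20% reduction is a ratio of 0.8, the SD of log stay is 0.2231 / 0.312 = 0.715.

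**Assumed inputs.** The article gives neither the share of outcome variance due to site (the ICC) nor the share due to severity. Both are varied over a range.

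**Closed form at 161 per arm**, with R² the variance share and 2.8016 = 1.960 + 0.8416:

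- true alpha, factor balanced by stratification but ignored: 2 × [1 − Φ(1.960/√(1 − R²))]
- unadjusted power, same case: Φ(0.8416/√(1 − R²))
- adjusted power: Φ(2.8016/√(1 − R²) − 1.960)

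| R² | true alpha if R² is all site | unadjusted power if R² is all site | adjusted power | n per arm for 80%, 161 × (1 − R²) |
|---|---|---|---|---|
| 0 | 5.0% | 80.0% | 80.0% | 161 |
| 0.05 | 4.4% | 80.6% | 82.0% | 153 |
| 0.10 | 3.9% | 81.3% | 84.0% | 145 |
| 0.20 | – | – | 87.9% | 129 |

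The alpha and unadjusted-power columns apply to site only. The adjusted column applies to site and severity together.

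**Simulation of the rank test.** 322 patients, 7 unequal sites, permuted blocks within site, lognormal stay with log SD 0.715, ratio 0.8; 6,000 null and 3,000 alternative replicates (Monte Carlo standard error about 0.3 and 0.7 points). Deaths are not modelled.

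| site ICC / severity R² | type I error, Wilcoxon | power, Wilcoxon | power, site-stratified Wilcoxon | power, linear model of log stay with site + severity |
|---|---|---|---|---|
| 0 / 0 | 4.8% | 77.8% | 76.8% | 79.4% |
| 0.02 / 0.05 | 4.9% | 77.9% | 77.7% | 82.7% |
| 0.05 / 0.10 | 4.6% | 79.0% | 79.3% | 86.3% |
| 0.10 / 0.10 | 4.2% | 80.1% | 81.6% | 88.0% |

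The stratified and adjusted tests had type I error of 4.5% to 5.2% throughout. Part of the last column's lead comes from the parametric model on lognormal data: with no site or severity effect it is already 1.6 points ahead of the Wilcoxon test.

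**Check on the remedy.** A smaller run of the same model (1,000 alternative replicates, standard error about 1.5 points) compared ways to adjust.

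| site ICC / severity R² | Wilcoxon, unadjusted | median difference in hours, unadjusted | median regression of hours, site + severity | site-stratified rank test adjusted for severity |
|---|---|---|---|---|
| 0.05 / 0.10 | 77.9% | 59.8% | 66.8% | 82.9% |
| 0.10 / 0.10 | 81.6% | 63.9% | 70.4% | 86.0% |

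Adjustment helps both approaches. But median regression used as the test has less power than even the unadjusted Wilcoxon test under lognormal stay, so the 82% to 88% does not carry over to it.

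**The case against.** - **The primary test is not expressly fixed.** The Wilcoxon clause follows the sentence on baseline comparisons, and for outcomes the section promises only median differences with intervals. This stands: a reader might infer that the article names the Wilcoxon test as the primary test, and it does not say so. It is, however, the only test offered for a skewed continuous variable.
- **Adjustment is commonly left to an analysis plan, which is not shown.** This stands in part. The plan may add site and severity. But the article names specific two-group procedures, and its subgroup section goes down to model terms, so the point concerns a stated method and not silence.
- **The size rests on assumed variance shares.** This stands. At a site share of 5%, simulated type I error is less than two Monte Carlo standard errors below 5%. The gain from severity needs APACHE II to predict stay. The article says baseline mortality is high; early deaths shorten stay in the sickest patients, so the relation may be weak or not monotone.
- **No planned power is lost.** This stands. The sample size mentions no adjustment, and the unadjusted rank test has about 78% to 80% power in simulation and 80% to 81% in closed form.

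A reader might also infer that omitting APACHE II makes the test conservative. It does not, since allocation is stratified by site only.

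**Conclusion.** The point holds as a modest weakness in efficiency and in matching analysis to design. Randomisation uses site, the named comparisons do not, and a baseline severity score already collected is left out of the main comparison.

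Ignoring site costs little: type I error of about 4.6% to 4.2% in simulation at an assumed site share of 5% to 10%. Stratifying the rank test by site alone changes power by between −1.0 and +0.3 points at an ICC up to 0.05 and by about +1.5 points at 0.10. Most of any gain depends on severity: with site and severity explaining an assumed 5% to 20% of variance together, power at 161 per arm is about 82% to 88% for a linear model of log stay.

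A reader might infer that the trial is underpowered or its primary result unsound because of this. The documents do not support that: the unadjusted test is valid, does not inflate false positives and keeps about its planned power. The mismatch and its direction are clear; its size is not known.

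**What to change.** Under Patient-centered analysis, state one primary analysis of ICU hours that accounts for the design, before unblinding. It should keep the median difference as the reported measure. Two forms do this:

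- a median regression of ICU hours on arm, with site as a factor and baseline APACHE II as a continuous covariate; or
- a site-stratified Wilcoxon (van Elteren) test with a site-stratified Hodges-Lehmann estimate.

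Given the power check above, I would take the p-value from the site-stratified rank test, adjusted for APACHE II by rank analysis of covariance, and use the median regression for the estimate and interval. Say which governs if the two disagree. Add a rule for pooling small sites and one for missing APACHE II. Keep the unadjusted comparison as a sensitivity analysis.

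The cost is wording and slightly more analysis work; site and APACHE II are already collected. Two trade-offs should be stated. The regression estimate is conditional on site and APACHE II. The Hodges-Lehmann estimate is a shift, which equals the difference in medians only if the two distributions differ by location alone.

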#### Health economic analysis

Analyses of the tertiary outcomes (i.e., health economic outcomes) will be based on health economic information obtained from public and private databases. Cost-effectiveness and cost-utility will be analyzed by estimating incremental cost and effectiveness based on ICU lengths of stay and average daily ICU costs. QALYs will be calculated based on health-related quality of life as measured by the EQ-5D-5L quality of life questionnaire. Further details of the health economic analysis will be presented separately.

### Pre-specified subgroup analyses

Secondary analyses will examine the effects for the length of ICU stay and duration of IV vasopressors within subgroups defined at baseline by age (< 65 vs. ≥65 years), sex, frailty (Clinical Frailty Scale score 1–4 vs. ≥5), severity of illness (quartiles of predicted risk of death from baseline APACHE II score), and types of shock (i.e., septic, hypovolemic, cardiogenic, obstructive or neurogenic). We will also evaluate subgroup based on comorbid conditions (i.e., pre-existing cirrhosis and acute kidney injury on admission). The subgroup analyses will use logistic regression with terms for treatment arm, subgroup, and subgroup by treatment interaction. We hypothesize that midodrine is more beneficial in young patients, in those with lower frailty and illness severity at baseline, those with pre-existing cirrhosis, those with acute kidney injury, and those who meet strict criteria for septic shock.

